## 11. Human research protection

### 11.1 Data confidentiality

Computer-based files will only be made available to study personnel through use of access privileges and passwords. Wherever possible, identifiers will be removed from study related information and analyses. Precautions will be in place for data security and HIPPA compliance.

## 11.2 Participant confidentiality

Information on participants will be obtained from the health system and will not be shared in a deidentified manner outside of the study team. The Ascension Data Science Institute (ADSI) will be the hub for data collection and evaluation. ADSI provides a secure platform with firewalls for management and evaluation of health system data including meeting standards for Health Insurance Portability and Account Act (HIPPA).

## 11.3 Participant privacy

All efforts will be made by study staff to ensure participant privacy. Data will be evaluated in a deidentified manner whenever possible.

## 11.4 Data disclosure

Information on patients will only be disclosed within the study team.

## 11.5 Data and safety monitoring

The Principal Investigator will closely monitor the safety, privacy and data integrity of the study.

## 11.6 Risk/benefit

### 11.6.1 Potential study risks

The main risk is data breach and as previously described precautions will be taken to minimize this risk

### 11.6.2 Potential study benefits

Successful approaches to encourage vaccination among more hesitant individuals could be important for other vaccination efforts to help address the COVID-19 pandemic

### 11.6.3 Risk/benefit assessment

There is minimal risk of breach of data and appropriate measures to reduce this risk have been taken. Given the potential benefits of the study, we believe the risk/benefit assessment is favorable.

# 12. Appendix

## 12.1 Text messaging script

### **Initial Text at 9am market time**

[First name Last name], Ascension is committed to providing a safe environment for associates, patients and visitors. All associates are required to receive the COVID-19 vaccine series by November 12, 2021. A dose is reserved for you on [insert day of the week or date, e.g. Monday, August 30, 2021].

Vaccine clinic locations and hours can be found here: [insert Market specific URL]

Reply Reschedule if you need to select a different date. Reply Upload if already vaccinated and you need to upload your vaccine card.

- If Reschedule: What day works best for you? Reply Monday, Tuesday, Wednesday, Thursday, or Friday.
  - You are confirmed for [insert day selected and reset appointment date in system]
  - If Other: Sorry, we did not recognize that response. You can text back Monday, Tuesday, Wednesday, Thursday, or Friday.
- If Upload: Submit your vaccination verification here; you will need your employee ID number and a photo of your vaccine documentation:  
<https://gdaintranet.ascension.org/home/covid-19-vaccine-external-documentation> [then stop text messages]
- If Other: Sorry, we did not recognize that response. You can text back Reschedule or Upload. If that day works for you, then you can visit any clinic within the hours they are open on that day. You may also receive vaccination from another site and Upload your vaccine care. If questions, email: [[contact]](mailto:[contact])

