## 3. Aims

### 3.1 Primary outcome

The percent of participants that receive the COVID-19 vaccine within 2 weeks of the intervention.

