### 5.3 Target population

Ascension Associates for whom the health system does not have documentation of COVID-19 vaccine or exemption from vaccination

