## 8.2 Procedures

Prior to the interventions, all Associates identified in the selected markets will be sent an email from Associate Health informing them of the upcoming text message intervention, that it will be staggered so some get it before others, and which phone number it will be sent from. Participants in the intervention arm will be sent up the following text messages (See Section 12.1 for full text message script).. Message 1 will inform them of Ascension's goal of keeping everyone safe during the pandemic, that a vaccine is reserved for them on a specific day, URL with vaccine clinic locations and times, and ability to either reschedule to another day, or obtain a link to upload documentation of vaccination. Message 2 will be sent the day before the scheduled date with vaccine clinic location and hours as well as allow them to reschedule, or

upload documentation if needed. Message 3 will be sent the morning of the date scheduled with vaccine clinic location and hours as well as allow them to reschedule, or upload documentation if needed. Message 4 will be sent the day after the date scheduled to ask if the vaccine was received or not. If yes, then the link for uploading documentation will be sent. If not they will be scheduled for another day and cycle back to Message 1. If the approach is found to be successful, participants in control will receive the same intervention about 2 weeks later.

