## 9. Analysis plan

Prior to analyses, we will produce data summaries to assess data quality, data distribution, and randomization success. All analyses will be evaluated using an intention-to-treat approach. An individual will be classified as vaccinated if they uploaded documentation of vaccination within 2 weeks after the end of the first week of vaccination appointments.

We estimate that a sample of 1450 (725 per arm) will provide at least 90% power to detect a 5 percentage point difference in vaccination between the intervention and control groups. This assumes a 20% vaccination rate in the control group and uses a two-sided alpha of 0.05.

The primary analysis will use a chi-square test to evaluate for differences in vaccination rate between the intervention and control group. Differences in time to vaccination will be evaluated using a t-test for means and Mann-Whitney test for medians. We will test the robustness of these findings by fitting a fully adjusted model with available participant characteristics. We will perform exploratory subgroup analyses for available participant characteristics.

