### **Day after appointment**

Did you receive the COVID-19 vaccine yesterday? Reply Yes or No

- If Yes: Thank you for doing your part to create a safe environment for our associates, patients and visitors. If you got the vaccine at a site other than Associate Health, please upload an image of your vaccine card here: <https://gdaintranet.ascension.org/home/covid-19-vaccine-external-documentation> [then stop text messages]
- If No: A COVID-19 vaccine is reserved for you next Monday. Locations and hours can be found here: [insert Market specific URL]
  - Reply Reschedule if you need to select a different day next week. Reply Upload if already vaccinated and you need to upload your vaccine card. [restart from top of logic]
- If Other: Sorry, we did not recognize that response. You can text back Yes or No. If questions, email: [[contact]](mailto:[contact])

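### Section 9 counts any upload of vaccination proof in the window as a primary event, whatever the dose or its date, and only the intervention arm is texted an invitation to upload older proof

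*Combined protocol and SAP*

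**What the plan says.** **Outcome.** Section 3.1 gives the primary outcome as "The percent of participants that receive the COVID-19 vaccine within 2 weeks of the intervention". Section 3.2 adds time to vaccination in days. Neither names a dose.

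**Rule used in the analysis.** Section 9 turns this into an upload rule, with the period running from the close of the first appointment week: "An individual will be classified as vaccinated if they uploaded documentation of vaccination within 2 weeks". It sets no dose number and does not require that the vaccination took place after launch.

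**Entry.** Section 5.3 targets Associates for whom the health system "does not have documentation of COVID-19 vaccine or exemption from vaccination". Section 5.5 repeats this and adds age. Neither mentions people who have had a dose that is not on file.

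**Script (Section 12.1).** The initial text reads "All associates are required to receive the COVID-19 vaccine series by November 12, 2021. A dose is reserved for you on" a given day, so it names a series and reserves one dose. The day-after text asks "Did you receive the COVID-19 vaccine yesterday? Reply Yes or No", and a yes leads to "then stop text messages". For a no, Section 8.2 says: "If not they will be scheduled for another day and cycle back to Message 1".

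**Upload route.** Section 5.1 lets previously vaccinated people in the intervention arm upload proof. The initial, day-before and same-day texts all offer an Upload reply for those already vaccinated. The control arm receives usual health system messaging, and no upload text is described for it.

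**The concern.** Receiving a vaccine in the window and uploading proof in the window are different events. Section 9 scores the second and Section 3.1 promises the first. They part in two cases:

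- **Vaccination before launch, never documented.** The person is eligible, uploads an old card and becomes an event. The texts prompted the paperwork, not the vaccination.
- **Undocumented first dose before launch, with a second dose already due.** The person takes it in the window, uploads and becomes an event that would have happened anyway.

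The second case should occur about equally in both arms and mainly dilutes the difference. The first need not be equal, because the text prompt to upload exists in one arm only. It can therefore create a difference in the primary outcome with no change in vaccination.

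The secondary outcome has the same gap. A pre-launch vaccination date gives a negative time, and an upload date gives time to paperwork.

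**Working it through.** **1. The passages side by side**

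| Item | Where | Unit | Date condition |
|---|---|---|---|
| Primary outcome | 3.1 | vaccine received | within 2 weeks of the intervention |
| Classification rule | 9 | upload of proof | on the upload only |
| Entry | 5.3, 5.5 | no proof or exemption on file | at implementation |
| Script | 12.1 | series required, one dose reserved | none |

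A card uploaded in the window that shows a pre-launch dose meets Section 9 and fails Section 3.1. Nothing in Section 5.3 or 5.5 keeps its holder out.

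**2. The plan's own figure**

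Inputs from Section 9: 725 per arm, 20% in control, a 5-point difference, two-sided alpha 0.05, chi-square test. Power = Φ[(d − 1.96·SE0)/SE1].

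- SE0 = √(2 × 0.225 × 0.775/725) = 0.02193
- SE1 = √[(0.20 × 0.80 + 0.25 × 0.75)/725] = 0.02189
- Power = Φ[(0.05 − 0.04299)/0.02189] = Φ(0.32) = 62.6%

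The stated 90% is not reproduced. That is a separate problem; 62.6% serves here only as the reference value.

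**3. False difference from unequal uploading**

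Let h be the share of the list with an undocumented pre-launch vaccination, and u_I and u_C the fractions of them who upload in the window. The false difference is h × (u_I − u_C). The documents give none of these values. The difference is zero if h = 0 or if uploading is equal, and it cannot exceed h. So h = 1% allows 0 to 1 point, h = 2% allows 0 to 2, and h = 5% allows 0 to 5.

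In people:
- The planned 5-point difference is 0.05 × 725 = 36.25 people.
- With 20% in control (145 of 725), 31 extra uploads in the intervention arm give 176 of 725. The difference is 31/725 = 4.3 points and the uncorrected chi-square p is 0.0499. With continuity correction it takes 33 (p = 0.043).

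**4. Dilution from second doses already due**

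Let m be the share of the list with an undocumented first dose and a second dose due. Assume 90% of them score as events in both arms and the rest follow 20% and 25%. Each rate is 0.9m + (1 − m)p, so the difference is 5(1 − m) points. Both m and the 90% are assumptions.

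| m | Control | Intervention | Difference (points) | Power, 725 per arm |
|---|---|---|---|---|
| 0% | 20.0% | 25.0% | 5.00 | 62.6% |
| 0.5% | 20.35% | 25.325% | 4.975 | 61.7% |
| 1% | 20.7% | 25.65% | 4.95 | 60.8% |
| 2% | 21.4% | 26.3% | 4.90 | 59.1% |
| 5% | 23.5% | 28.25% | 4.75 | 54.2% |
| 10% | 27.0% | 31.5% | 4.50 | 46.9% |
| 20% | 34.0% | 38.0% | 4.00 | 35.4% |

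Up to m = 2% the loss is at most 3.5 percentage points of power.

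**The case against.** The best defence is that the plan uses one term at both ends. A person enters without documented vaccination and becomes an event when documentation arrives. If any dose record counts at entry and at outcome, a person with a recorded first dose is off the list and the event is roughly the first documented dose. This reading is natural, and it stands. It limits the problem to doses that HR does not hold, possibly very few. It does not remove the problem: the first documented dose can still predate launch, and the texts ask for exactly that document.

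Randomization balances earlier doses between arms. That is true, and it makes second doses already due a matter of dilution. It does not balance the prompt to upload.

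A reader might go further and infer from the word series that only a completed series counts, so that people who start on the reserved date are scored as failures. The documents do not support this. The word occurs only in the initial text. Sections 1 and 4 state the mandate simply as obtaining the vaccine, and the later texts treat one visit as the unit. The supposed loss of events also needs a dose interval and a product mix that the documents do not give.

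**Conclusion.** The point holds as a mismatch between Section 9 and Section 3.1. As written, uploads that show a pre-launch dose or a second dose already due are primary events, and the one-sided upload prompt can turn the former into a difference in favour of the intervention.

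The size cannot be stated. It depends on how many people on the list have undocumented earlier doses and how much more often they upload when texted. Both are absent from the documents, and the effect may be near zero if HR records are complete. The 31-person figure shows how few uploads would matter, not how many to expect. The higher rows of the dilution table are assumptions, not estimates.

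Two stronger conclusions might be inferred and are not supported: that every reading of the endpoint fails, since the consistent reading in the objection comes close to a sound one; and that bias is established, since the documents show the route and not its use. Even so, the correction is worth making because it is cheap and should be settled before data by arm are seen.

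**What to change.** - In Sections 3.1, 3.2 and 9, define the event in both arms as a first documented COVID-19 vaccine dose whose recorded vaccination date falls after launch and inside the window.
- Count a record showing a first dose dated before launch as a non-event in both arms, and keep everyone randomized in the denominator. Removing such people after randomization would remove more of them from the arm that is prompted to upload.
- Measure time in Section 3.2 to the recorded vaccination date, not the upload date.
- Word the conclusion as starting vaccination.
- The sponsor should reconcile the script's series and single-dose wording with the outcome wording. Which dosing requirement applies is for the sponsor to state.

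Cost: dose number and date must be read from the card or clinic record in both arms, and the claim becomes narrower (first dose). No participants or visits are added. The date condition does not equalise prompting for doses truly received after launch; that limitation remains and should be stated.

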### **Example Screenshot**

[figure not shown]

**One day before scheduled date at 9am market time**

A COVID-19 vaccine is reserved for you tomorrow. Locations and hours can be found here:  
[insert Market specific URL]

Reply Reschedule if you need to select a different day next week. Reply Upload if already vaccinated; you need to upload your vaccine card.

- If Reschedule: What day works best for you? Reply Monday, Tuesday, Wednesday, Thursday, or Friday.
  - You are confirmed for [insert day selected and reset appointment date in system]
  - If Other: Sorry, we did not recognize that response. You can text back Monday, Tuesday, Wednesday, Thursday, or Friday.
- If Upload: Submit vaccination verification here; you will need your employee ID number and a photo of your vaccine documentation: <https://gdaintranet.ascension.org/home/covid-19-vaccine-external-documentation> [then stop text messages]
- If Other: Sorry, we did not recognize that response. You can text back Reschedule or Upload. If that day works for you, then you can visit any clinic within the hours they are open on that day. You may also receive vaccination from another site and Upload your vaccine care. If questions, email: [[contact]](mailto:[contact])

**Example Screenshot**

[figure not shown]

### **Morning of Day scheduled at 9am market time**

A COVID-19 vaccine is reserved for you today. Locations and hours can be found here: [insert Market specific URL]

Reply Reschedule if you need to select a different day next week. Reply Upload if already vaccinated and you need to upload your vaccine card.

- If Reschedule: What day works best for you? Reply Monday, Tuesday, Wednesday, Thursday, or Friday.
  - You are confirmed for [insert day selected and reset appointment date in system]
  - If Other: Sorry, we did not recognize that response. You can text back Monday, Tuesday, Wednesday, Thursday, or Friday.
- If Upload: Submit vaccination verification here; you will need your employee ID number and a photo of your vaccine documentation: <https://gdaintranet.ascension.org/home/covid-19-vaccine-external-documentation> [then stop text messages]
- If Other: Sorry, we did not recognize that response. You can text back Reschedule or Upload. If that day works for you, then you can visit any clinic within the hours they are open on that day. You may also receive vaccination from another site and Upload your vaccine care. If questions, email: [[contact]](mailto:[contact])

### **Example Screenshot**

[figure not shown]

### **Day after appointment**

Did you receive the COVID-19 vaccine yesterday? Reply Yes or No

- If Yes: Thank you for doing your part to create a safe environment for our associates, patients and visitors. If you got the vaccine at a site other than Associate Health, please upload an image of your vaccine card here: <https://gdaintranet.ascension.org/home/covid-19-vaccine-external-documentation> [then stop text messages]
- If No: A COVID-19 vaccine is reserved for you next Monday. Locations and hours can be found here: [insert Market specific URL]
  - Reply Reschedule if you need to select a different day next week. Reply Upload if already vaccinated and you need to upload your vaccine card. [restart from top of logic]
- If Other: Sorry, we did not recognize that response. You can text back Yes or No. If questions, email: [[contact]](mailto:[contact])

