## 5. Study Design

### 5.1 Design

This will be conducted as a two-arm randomized, controlled trial. The control arm will receive usual health system messaging about the importance and deadlines for receiving COVID-19 vaccination. The intervention arm will receive a text message stating that the vaccine is reserved for them on a specific date. They will have the ability to reschedule to a different day, opt-out of this text messaging intervention, or if previously vaccinated they can upload documentation to the Ascension website.

A list of Associates for whom Ascension does not have documentation of vaccination or exemption from vaccination will be provided by Human Resources at Ascension. Information on vaccine clinic locations and hours are available online and a link to them will be provided in the text message.

Participants sites will likely include Ascension Associates from the following markets: DC, Maryland, NY Binghamton, Kansas and/or Florida

The trial is anticipated to begin around: September 13, 2021.

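### Section 9 scores vaccination by upload alone, but the script requests uploads only for doses given outside Associate Health, so in-house doses may go uncounted

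*Combined protocol and SAP*

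**What the plan says.** - **Outcome.** Section 3.1 names it as "The percent of participants that receive the COVID-19 vaccine within 2 weeks of the intervention". This is receipt of a dose, not proof of it.
- **Scoring rule.** Section 9 makes it operational: "An individual will be classified as vaccinated if they uploaded documentation of vaccination", with the upload falling in the stated period. No second source is mentioned.
- **Day-after text (Section 12.1).** A participant who replies Yes is told: "If you got the vaccine at a site other than Associate Health, please upload an image of your vaccine card here". Texting then ends.
- **Earlier texts (Section 12.1).** The general invitation does not mention a site: "Reply Upload if already vaccinated and you need to upload your vaccine card". The reply to an unrecognised response ties the upload to an outside dose: "You may also receive vaccination from another site and Upload your vaccine care". The address of the upload page also describes it as being for external documentation.
- **Procedures.** Section 8.2 summarises the day-after step without a site condition: "If yes, then the link for uploading documentation will be sent".
- **Control arm.** Section 5.1: "The control arm will receive usual health system messaging about the importance and deadlines for receiving COVID-19 vaccination". The documents do not say whether that messaging asks for uploads.
- **Records.** Section 5.1: "A list of Associates for whom Ascension does not have documentation of vaccination or exemption from vaccination will be provided by Human Resources". The system therefore holds some vaccination documentation. No section says how doses given at its own clinics enter that record, or whether they count towards the outcome.

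**The concern.** The scoring rule depends on an action that the script does not ask of everyone who is vaccinated. Someone who is vaccinated at Associate Health, replies Yes and follows the text has no reason to upload anything. That person meets the outcome in Section 3.1 but not the classification in Section 9.

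The gap is in the primary endpoint. Under an upload-only rule the comparison mixes two things, getting vaccinated and filing proof, and the intervention may change both. The texts may affect where people go for the dose, and they prompt uploads. The observed difference could therefore be smaller or larger than the true difference in vaccination.

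**Working it through.** **Inputs from Section 9.** 725 per arm, 20% vaccinated in control, a 5-point difference (so 25% under intervention), two-sided alpha 0.05, chi-square test.

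**Assumed inputs.** The documents give neither of these:
- f, the share of in-window doses given at Associate Health;
- u, the share of those recipients who upload anyway.

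Outside doses are taken as always uploaded.

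**Step 1. The plan's own figure.** Power = Φ{[d√n − 1.96√(2p̄(1−p̄))] / √(p₁(1−p₁) + p₂(1−p₂))}.
- With d = 0.05, n = 725 and p̄ = 0.225, the numerator is 1.346 − 1.157 = 0.189.
- The denominator is √0.3475 = 0.589, so power = Φ(0.320) = 62.6%.
- The stated figure is at least 90%. That shortfall is a separate matter. The 62.6% serves here only as the no-loss reference.

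**Step 2. Observed rate under the upload rule.** Observed rate = true rate × capture, where capture = 1 − f(1 − u).

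**Step 3. Equal loss in both arms.**

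| f | u | Control | Intervention | Difference (points) | Power at 725 per arm |
|---|---|---|---|---|---|
| 0 | – | 20.0% | 25.0% | 5.0 | 62.6% |
| 25% | 0 | 15.0% | 18.75% | 3.75 | 47.9% |
| 30% | 0 | 14.0% | 17.5% | 3.5 | 44.8% |
| 50% | 0 | 10.0% | 12.5% | 2.5 | 32.5% |
| 50% | 50% | 15.0% | 18.75% | 3.75 | 47.9% |

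The risk ratio stays at 1.25. The absolute difference and the power both fall.

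**Step 4. Steering towards in-house clinics (u = 0).** Let 30% of control doses be lost, which is 0.30 × 20 = 6 points.
- Suppose every one of the 5 extra points under intervention is in-house and not uploaded. The loss is then 6 + 5 = 11 of 25 points (44%), and the observed rates are 14.0% versus 14.0%. The effect is hidden but not reversed.
- The sign reverses only when intervention capture falls below 0.20/0.25 = 80% of control capture. A 50% intervention loss gives 12.5% versus 14.0% in control. It requires 12.5 lost points, of which at most 5 can be the extra doses. The other 7.5 come from the baseline 20 points, so the in-house share of those must rise from 30% to 7.5/20 = 37.5%. The texts would have to divert people who would have been vaccinated elsewhere.

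**Step 5. Prompts in one arm only.** Take f = 50% in both arms, u = 0 in control and u = 50% under intervention. Capture is 1 − 0.5 = 0.50 in control and 1 − 0.5 × 0.5 = 0.75 under intervention.
- With no true effect (20% in both arms), the observed rates are 10.0% versus 15.0%, a spurious 5 points.
- With the planned effect, they are 10.0% versus 0.75 × 25 = 18.75%, an apparent 8.75 points instead of 5.

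Steps 4 and 5 point in opposite directions, and the documents give no basis for choosing between them.

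**The case against.** The strongest answer is that Section 9 is loosely worded and the design is sound. It says that a person is vaccinated if they uploaded. It does not say only if. Sections 5.1, 5.3 and 5.5 define status by what documentation the health system holds. The day-after text asks only outside recipients to upload, through a page labelled as external. The coherent reading is that in-house doses are already known to the system and that uploads fill in the rest.

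That reading is plausible. A reader might therefore go too far in inferring that in-house doses were certain to be scored as failures: that follows from the rule taken literally, not from any statement of intent. But no section says that those doses count. The rule for a primary endpoint should not have to be inferred, and Section 9 is the only rule given.

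Three further inferences are tempting and not supported:
- **That the loss necessarily works against the intervention.** The texts link to market-specific clinic lists without saying which clinics are Associate Health. Section 5.1 says that clinic information is also online, so controls can use the same sites. The scripted upload prompts go only to the intervention arm, which could bias the result the other way.
- **That the sign would reverse.** This needs diversion from other sites as well as loss of the extra doses, and every share used is assumed.
- **That Section 8.2 and the script flatly contradict each other.** The Yes reply shows the link to everyone, and only the accompanying request is conditional. The mismatch is minor, and it means that some in-house recipients may upload.

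**Conclusion.** Wrong as written. Followed exactly, the Section 9 rule leaves out Associate Health doses without a voluntary upload, although Section 3.1 counts them as events. This conclusion rests on the text and needs no assumed figure.

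The size and direction of the bias cannot be determined from the documents. Everything numerical beyond the Section 9 inputs depends on assumed in-house shares and upload rates, so the results show what could happen and are not estimates. If the analysts in fact count in-house doses from system records, those doses are not lost and the defect is confined to the written plan. It should still be corrected there.

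**What to change.** In Section 9, define a participant as vaccinated if a dose dated within the outcome window is shown by either the Associate Health administration record or uploaded documentation. State that both sources are linked to the randomised list in the same way for both arms. Take the dose date for the time-to-vaccination outcome from the same two sources. Then make Sections 3.1, 8.2 and 9 and the day-after text agree on what counts and on who is asked to upload.

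The cost is one sentence in the analysis plan and a data link. This assumes that Associate Health keeps records of the doses it gives, which is likely but not described in the documents. No change to sample size or follow-up is needed. With in-house doses counted and outside doses taken as always uploaded, capture returns to 1 and the planned contrast is again 20% versus 25%.
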